## Abstract

### Background

Adolescents represent a growing share of people living with HIV in sub-Saharan Africa (SSA), yet they have lower engagement in care, poor adherence to medication and viral suppression (VS) compared to adults due to a high mental health burden they experience. We postulate that to achieve optimal adherence, interventions that promote mental health and are tailored to the dynamic social and cognitive needs of adolescents as they pass through life stages need to be tested and promoted. Mindfulness and acceptance-based interventions are slowly gaining traction as appropriate for adolescents.

### Purpose

This study adapts and explores the acceptability of mindfulness and acceptance-based psychosocial intervention (acceptance and commitment therapy-ACT-Discoverer, noticer, advisor-values model-DNA-v), among providers (health care practitioners -HCPs) and users (adolescents living with HIV/AIDS). Further, it endeavours to measure the feasibility and effectiveness of ACT-DNA-v in reducing psychosocial barriers /mental health challenges (anxiety, depression & stigma) among adolescents living with HIV (ALWHAs). The study will be carried out at two Kampala Capital City Authority-KCCA health centres (Kisenyi and Kitebi) with ALWHA and their HCPs.

### Methods

Sequential multi-methods design will be used, commencing with a formative phase where ACT-DNA-v will be adapted to fit the specific needs of users and providers in Kampala and using semi-structured interviews, explore the acceptability of ACT-DNA-v among users and providers, as well as implementation related factors. This phase will be followed by measuring the feasibility and effectiveness of the adapted ACT-DNA-v in improving mental health outcomes among ALWHA with a randomized control trial (RCT). The trial will involve quantitative surveys at baseline, post-intervention and follow-up, testing the effects of the intervention on process and clinical outcomes among ALWHA. Thematic analysis that involves coding, analysis and interpretation of findings utilizing qualitative data analysis software (QDA) will be used for the qualitative study, while T-test, Fisher's exact, regression, Chi-square tests and analysis of variance (ANOVA) respectively will be used in the quantitative phase to ascertain average mean differences between the two study groups on the outcome parameters of depression symptoms, anxiety, and stigma at pre-post intervention and psychological flexibility at follow-up.

### Utility of findings

Study findings will be used to justify the integration of mindfulness and acceptance into psychosocial support services offered to adolescents living with HIV.

## List of abbreviations

**ACT:** Acceptance and Commitment Therapy

**AFQ-Y:** Avoidance and Fusion Questionnaire for youth

**AIDS:** Acquired Immunodeficiency Syndrome.

**ALWHA:** Adolescents Living with HIV/AIDS

**ANCOVA:** Analysis of Covariance

**ART:** Antiretroviral Therapy.

**CBTs:** Cognitive Behavioral Therapies

**DNA-v:** Discoverer, Noticer and Advisor-values model

**FGDs:** Focus Group Interviews

**HBM:** Health Belief Model

**HCPs:** Health Care Providers (Counselors)

**HIV:** Human Immunodeficiency Virus.

**IARSS:** Internalized AIDS-Related Stigma Scale

**IDI:** In-Depth Interviews

**KCCA:** Kampala Capital City Authority

**KHCIV:** Kisenyi Health Center IV

**KTHCIII:** Kitebi Health Center iii

**RFT:** Relational Frame Theory

**SAS-A-SF:** Social anxiety scale for adolescents, short version.

**SOM-REC:** School of Medicine Research and Ethics Committee.

**SSA:** Sub-Saharan Africa

**UNCST:** Uganda National Council for Science and Technology.

**VLS:** Viral Load Suppression

## Operational Definitions

**ACT:** Third wave cognitive behavioral therapy that combines mindfulness, acceptance, values clarification and behavioral goal setting to improve wellbeing through a process called psychological flexibility. ACT fosters psychological flexibility through six sub-processes; experiential acceptance, contact with the present moment, defusion, self-as-context, values, and committed action .

**DNA-v:** An evidence-based model that promotes psychological strength, values consistent living, vitality, and success. It is designed to help young people cope with challenges, stress, and change. DNA-V is a combination of Acceptance and Commitment Therapy (ACT) and positive psychology, and is underpinned by contextual behavioral science .

**Adolescent:** The World Health Organization (WHO) defines an adolescent as someone within the age range of 10 years – 19 years. For this particular study, we shall focus on older adolescents 15 – 19 years of age .

**Psychological Flexibility:** Contacting the present moment fully as a conscious human being, and based on what the situation affords, changing or persisting in behavior in the service of chosen values.

**Cognitive fusion:** Process that involves attaching a thought to an experience. This results in entanglement and believing thoughts as if they are real. The mindfulness and acceptance intervention is targeted at creating a detachment between thoughts and experiences .

**Mindfulness:** Being intensely aware of what you're sensing and feeling in the moment, without interpretation or judgment .

**Acceptability:** Exploring perceptions and experiences of providers (HCPs) and users (adolescents) regarding the intervention. Exploration will be done following the 7 domains of the theoretical framework for acceptability (TFA; affective attitude, burden, perceived effectiveness, ethicality, intervention coherence, opportunity cost and self-efficacy . Narratives from providers and users will determine if the intervention is acceptable.

**Feasibility:** Degree of convenience for use. If 70% of participants contacted consent/assent to participate, are retained in study for 6 months, adhere to the protocol, complete at least 4 out of 6 sessions and assignments, and recruitment happens in one month as planned, then intervention will be considered feasible .

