##### *Inclusion Criteria:*

Participant should be 15-19 years of age, diagnosed HIV positive, attending care at Kisenyi Kitebi health center for the last 6 months, on first or second line of treatment, can speak/understand

Luganda or English and willing to provide informed consent/assent. All records will be confirmed via clinic medical charts.

*Exclusion criteria:*

A participant will not be eligible to be part of the study if he/she plans to move out of the catchment area within six months, or if he/she is participating in another study related to HIV and care improvement.

*Sampling for sub-study two*

*Sample size*

The following assumptions are considered for determining the appropriate sample size for the quantitative study.

Assumptions:

$$N = 2 \frac{[Z\alpha + Z\beta]^2 S^2}{(\mu_1 - \mu_2)^2}$$

where:

$Z\alpha$  is standard normal value corresponding to level of significance

$Z\beta$  is standard normal value corresponding to power of the study

$\alpha$ =acceptable type 1 error

$\beta$ = type II error

$\mu_1$  is mean in control group and  $\mu_2$  is mean intervention

$\mu_1 - \mu_2$  =effect size (minimum meaningful difference between the means in the control and intervention groups)

$S$ =standard deviation of the outcome in the control group

$N$  is the sample size per group

$Z\alpha = 1.96$ ,  $Z\beta = 0.84$ ,  $\alpha = 0.05$  in 2 tails,  $\beta = 0.20$  (at 80% power).

Considering a study evaluating effectiveness of Acceptance and Commitment Therapy (ACT) on reducing the depressive symptomatology among Swedish and Australian adolescents (Livheim et.al, 2015), the difference in means of the post treatment RADS2 scores between the ACT arm and control arm was 4.09 while the standard deviation in the control arm was 5.13.

Substituting into the formula,

$$N = (2(1.96 + 0.84)^2 \times 5.13^2) / (4.09^2)$$

$$N = 25.1$$

N=26 participants in each group

If we consider a possible clustering in any of the two sites and a design effect of 2.0, the new minimum sample size is  $26 \times (2) = 52$ . If we consider a 10% loss to follow-up, the revised sample size will become  $(52 \times (1 / (1 - 0.10))) = 58$  participants. We, therefore, aim to recruit, **a total of 116 participants** at 80% power of detecting a mean difference of 4.09 or more in the intervention.

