#### Sampling method

To obtain participants for the Quantitative study, convenience sampling will be used at the screening stage, adolescents will be approached for potential enrollment into the study. Only those who consent/assent will be enrolled. Consent from guardians will also be sought for participants below the age of 18.

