#### Data collection and measures

For feasibility assessment: observation, checklists and survey will be used to collect data. The feasibility measures will include; i) enrollment (number of ALWHA's referred, proportion of those who are eligible and the number that consent), ii) attendance (number of sessions attended and completed and reasons for non-attendance iii) Retention in the study (number of participants completing all sessions and assignments) iv) number of assessments completed and missing data and v) self-rated program acceptability (helpful, meaningful, relevant and interesting).

When evaluating the effectiveness of a mindfulness and acceptance-based intervention, standardized survey instruments and document review will be used to collect data at baseline and post-intervention respectively.

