|-----------------------------------------------------------------------|------------------------------------------------------------------------------------------------------------------------------------------------|-----------|---------------------------------------------------------------------------------------------------------------------------------------------------------------------------------------------------------------------------------------------------------------------------------------------------------------------------------------------------------------------------------------------------------------------------------------------------------------|-------------------------------------------------------------------------------------------------------------------------------------------------------------------------------------------------------------------------------------------------------------------------------------------------------------------------------------------------------------------------------------------------|
| To adapt and measure the feasibility of ACT-DNA-v for use with ALWHA. | *Enrollment
*Attendance
*Retention in the study.
*Completion of sessions and assignments.
*Assessments completed and missing data. | ALWHA     | *Number of ALWHA's referred, the percentage who are eligible and the number consented.
*Number of sessions attended and reasons for non-attendance.
*Number of participants who stay in the study till the end (screening baseline, intervention & follow-up) and reasons for withdrawal.
*Number of participants completing all assessments (including participant feedback regarding acceptability of data collection methods, duration& content). | *Analysis; Descriptive statistics; summarizing recruitment, demographics, attendance, attrition and intervention adherence.
*Outcomes will include; % of participants consented out of those contacted, % of participants retained, % of participants completing all sessions, % of participants completing assignments, % of participants dropping out of study and reasons for withdrawal. |

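### The 70% consent criterion for feasibility rests on an undefined denominator of adolescents contacted, chosen by convenience, so eligibility losses or selection can move the result across the threshold

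*Protocol*

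**What the plan says.** Feasibility is the second research objective, and the Operational Definitions give it a decision rule. The rule begins "If 70% of participants contacted consent/assent to participate, are retained in study for 6 months, adhere to the protocol" and continues "complete at least 4 out of 6 sessions and assignments, and recruitment happens in one month as planned, then intervention will be considered feasible". Consent is thus one of several conditions that must all be met.

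Table 2, under Outcome measures, lists the matching outcome as the percentage "of participants consented out of those contacted". The Sampling method section describes how contacts arise: "convenience sampling will be used at the screening stage, adolescents will be approached for potential enrollment into the study". It names no order, register or consecutive rule.

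The section on Data collection and measures records recruitment in separate steps: "number of ALWHA's referred, proportion of those who are eligible and the number that consent". Table 2 lists the same steps. The 70% threshold is not tied to the eligible count. Among the inclusion criteria is being "willing to provide informed consent/assent". The exclusion criteria cover adolescents who intend to leave the area within six months and those already in another HIV study.

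**The concern.** A consent threshold is meant to show whether adolescents who could join are willing to. Here the denominator is everyone contacted, a term the protocol does not define. A planned move or membership of another study would usually emerge only in conversation, that is, after contact. An adolescent excluded on that ground never gets the chance to consent, yet stays in the denominator if contacted is read in the ordinary way. Ineligibility is then counted as refusal.

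The numerator has its own weakness. With convenience sampling, the consent rate describes whichever adolescents staff happened to approach. Nothing in the protocol links that group to the roughly 480 adolescents in the study population.

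At stake is a threshold set in advance. Because the conditions are joined by *and*, a rate just under 70% would by itself prevent ACT-DNA-v from being called feasible, even if uptake among adolescents able to join were well above 70%.

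**Working it through.** **Inputs**
- Threshold: 70% of those contacted (Operational Definitions). It is stipulated, so there is no derivation to reproduce.
- Recruitment target: 116 (Sample size).
- Study population: about 480 (Study population, sub-study two).
- Share of contacts who are eligible, *e*: not given. I assume a range of 0.70 to 1.00. *Eligible* here means meeting every criterion other than willingness to consent.

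**Effect of ineligible contacts**

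Rate among contacted = *e* × (consent among eligible). To read 70%, consent among eligible must equal 0.70 / *e*.

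| Eligible share *e* | Consent needed among eligible | Rate recorded if 80% of eligible consent |
|---|---|---|
| 1.00 | 70.0% | 80% |
| 0.95 | 73.7% | 76% |
| 0.90 | 77.8% | 72% |
| 0.85 | 82.4% | 68% |
| 0.80 | 87.5% | 64% |
| 0.75 | 93.3% | 60% |
| 0.70 | 100% | 56% |

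Below *e* = 0.70 the criterion cannot be met at all. With 80% uptake among eligible adolescents, the recorded rate crosses the threshold when *e* drops below 0.70 / 0.80 = 0.875. The effect runs one way: ineligible contacts can lower the rate but cannot raise it.

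**One data set, two denominators (illustrative)**

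Suppose 170 are contacted, 136 of them (80%) meet all criteria other than willingness, and 116 consent.
- Per contacted: 116 / 170 = 68%, below the threshold.
- Per otherwise eligible: 116 / 136 = 85%, above it.

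**How far selection could matter at the extreme**

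116 / 0.70 = 165.7. So 116 consents from 165 contacts pass (70.3%) and 116 from 166 fail (69.9%).
- A pass at 116 of 165 is compatible with uptake across the 480 as low as 116 / 480 = 24%, if everyone not contacted would refuse.
- A fail at 116 of 166 leaves 50 refusals. It is compatible with uptake as high as (480 − 50) / 480 = 90%, if everyone not contacted would accept.

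These are outer bounds, not expected errors. They show only that convenience sampling supplies nothing to narrow them.

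**The case against.** No sentence in the protocol says that ineligible adolescents are in the denominator. The inclusion criteria say records will be checked against clinic charts, and time in care and treatment line are things a chart could show, so part of the screening might come before contact. The eligible share is assumed; at 90% to 95% the bar moves only from 70% to between 74% and 78%. Numbers referred, eligible and consenting are collected anyway, and the protocol commits to CONSORT 2010 reporting, so a reader of the results could separate ineligibility from refusal. Consent among all contacted is also a legitimate, stricter measure of reach, and convenience recruitment is openly stated.

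Much of this stands. It makes the defect an undefined term rather than a stated error, and it limits the likely size. It does not remove the problem: the charts are not said to be checked before contact, some exclusions need a conversation, and the 70% rule is not attached to the eligible count even though that count is collected.

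A reader might go further and infer that the verdict can pass or fail whatever the true uptake. The protocol does not support that. If contacts were all eligible and behaved like a random sample, the chance of at least 116 consents in 165 would be 0.004 at 60% uptake, 0.09 at 65%, 0.51 at 70%, 0.93 at 75% and 0.999 at 80%, so the criterion does track uptake. Nor can consent alone deliver a pass, since retention, adherence to the protocol, session completion and one-month recruitment are also required. Deliberate choice of likely consenters is likewise conjecture; the text only leaves the choice open.

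**Conclusion.** The point holds as a defect in how the consent criterion is fixed. The denominator is undefined relative to eligibility screening, and the contacts are an unstructured convenience sample. On the ordinary reading of *contacted*, late-discovered ineligibility biases the rate downwards: the real bar becomes 78% if 90% of contacts are eligible and 88% if 80% are. Those shares are assumptions. Selection can move the rate either way by an amount that cannot be estimated from the protocol. The consequence is asymmetric, because a consent shortfall can veto feasibility but a consent pass cannot confer it. This is a cheap improvement to a pre-set decision rule, not a flaw that undermines the trial.

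**What to change.** In the Operational Definitions and Table 2, define the criterion as the number consenting divided by the adolescents approached who meet all inclusion and exclusion criteria other than willingness to consent. That qualifier is needed: willingness is itself an inclusion criterion, so a plain ratio of consented to eligible would approach 100% and test nothing. Report the whole flow: referred, screened, eligible, approached, consented.

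In Sampling method, replace convenience sampling with approaching consecutive attenders aged 15 to 19, or working through the clinic register in a pre-set order, at both sites, until 116 are enrolled. Log every approach.

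At 70% uptake, 116 / 0.70 gives about 166 eligible adolescents approached, out of about 480. If only 80% of those screened were eligible, that would mean screening about 166 / 0.80 = 208. No extra participants or procedures are needed. The cost is protocol wording, a screening log (much of which is already planned) and some loss of staff freedom over whom to approach. It should be settled before recruitment starts, because approaches that were not logged cannot be reconstructed.

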## Introduction

In sub-Saharan Africa (SSA), where 82% of the global HIV-positive young people live, adolescents are persistently among the most at-risk populations (MARPs) for HIV. In Uganda which is 10th among SSA countries with the highest HIV prevalence (6.7%), an estimated 1.4 million people are living with HIV/AIDS (PLHIV). The HIV prevalence in Uganda is even higher among young people, who presented about 19% of all new HIV infections in 2015. With many children born with HIV reaching adolescence in concurrence with the youth bulge in SSA, the importance of contextually appropriate HIV care and prevention strategies focused on adolescents living with HIV/AIDS (ALWHA) needs to be emphasized. In Uganda specifically, 34.8% of the population is between 14-24 years of age; the same group also accounts for almost 50% of HIV cases, warranting a focus on this vulnerable group.

Despite efforts to improve HIV care among ALWHA in SSA, current interventions have not optimized the intended impact. In Uganda, young people continue to be the only group with increasing HIV-related mortality amidst general declines in other groups. Among the individual, interpersonal, community and health systems challenges, the increase in morbidity has been attributed to poor medication adherence among young ALWHA. Successful antiretroviral therapy (ART) programs are highly dependent on adherence to medication and sustained care engagement; further, slowed progression to AIDS, sustained viral load suppression (VLS), reductions to ART resistance, and lengthened survival rates are achieved through maintenance of a >95% daily oral dosing of ART. Studies using medication possession ratios and clinical counts have found a higher proportion of older people to be more adherent to medical regimens compared to adolescents (72% adherence among adults compared to 68% adherence among young people). Furthermore, VLS data, a key indicator of medication success among PLHIV, shows that in 2017, only 39.6% of young people had achieved VLS, compared to 74.2% of adults.

Barriers to ART adherence among ALWHA include socio-economic (poverty, lack of food, loss of parents, and school environment), psychosocial and individual (perceived and experienced anxiety, fear, discrimination, lack of family support, peer influence, depression, privacy concerns in schools & stigma), and treatment-related factors (drug fatigue, pill burden, lack of clinical support, medication side effects and distance to health facilities). Although a clear categorization of barriers exist, psychosocial factors are often embedded within other barriers and seem predominant among ALWHA since they are exacerbated by the onset of puberty.

The unique developmental changes at the onset of puberty play an important role in shaping perceptions, beliefs, attitudes, self-efficacy, evaluation of severity of disease and pathways to care. Biologically, the start of puberty remodels the brain's dopaminergic system, resulting in increased risk-taking, emotionality, and egoistic tendencies, making adolescence a time of

heightened vulnerability to risk and reckless behaviors such as taking medication holidays . Adolescence is further complicated by self-regulatory challenges, preference for immediate gratification, exploration, secretiveness and concrete thinking ; this period also coincides with changes in the social environment, such as spending less time with parents and more with peers, as well as an increase in autonomy . A combination of these changes affects psychosocial pathways to health by inducing increased entanglement with thoughts (cognitive fusion) and continuous attempts to control thought experiences (experiential avoidance), resulting in psychopathological experiences such as depression, anxiety, and internalized stigma; these factors are documented causes of ART non-adherence among ALWHA . Since psychosocial challenges impact all aspects of treatment among ALWHA , there is a need to promote developmentally appropriate and culturally sensitive psychosocial support interventions (PSI) if treatment efficacy is to be improved in this population. The shortage of such interventions will continue to undermine other structural or health systems-level efforts to improve health outcomes among ALWHA.

Psychosocial support interventions such as; short message services (SMS), cognitive behavioral group therapy services, individual counselling, individual + group counselling, treatment supporters , Suubi+  and many others, have been posited to promote ART adherence among PLHIV in Uganda. However, interventions that resonate with the unique needs of adolescence as a developmental stage are scarce . Further, a majority of these previously tested interventions were designed for adult populations, and research has shown that adult-focused interventions have limited utility and efficacy among young people. Further, many of the reviewed interventions such as SMS are costly to sustain with adolescents , and have been implemented without adaptation and the mechanism of their proposed action and resulting behavior change, remains unclear, limiting replicability and scalability .

Evidence-based, contextually appropriate and theory-informed psychosocial interventions focused on targeted pathways that address adolescent's complex demands need to be adapted, developed and tested to improve optimal adherence in resource-limited settings like Uganda .

Mindfulness and acceptance-based psychosocial interventions are increasingly gaining traction as appropriate and effective support interventions for young people. These interventions focus on increasing self-regulation of attention and with curiosity, openness and acceptance as a way of dealing with painful thoughts, feelings and conditions. Developmental changes in adolescence are mostly impacted by emotions, yet executive functions such as judgement impulse control and emotion regulation are still underdeveloped. Since mindfulness can regulate emotions, it can counteract this imbalance. Acceptance and Commitment Therapy (ACT), is one particular mindfulness-based intervention that has produced promising results when used with adolescents with chronic conditions.

ACT is an intervention that improves mental health through psychological flexibility. Considered as part of the “third wave” Cognitive Behavioral Therapies (CBTs), ACT focuses on context sensitivity and functions of psychological phenomenon. It aims to change the function of events and relationships individuals develop with events using metaphors and experiences that support psychological flexibility. ACT-based interventions have been shown to improve quality of life and mental health among adults LWHIV and young people with chronic diseases. It has also proved to be feasible and acceptable among adults living with HIV/AIDS; however, no study has assessed its relevance and appropriateness for ALWHA.

One particular ACT model that is used with young people is the; Discoverer, Noticer and Advisor-Values model (DNA-v model). This model integrates three functional classes of skills to promote psychological flexibility, the main tenant of ACT-based therapies. DNA-v is based on the assumption that, unlike adults, young people have limited well-established values to guide behaviours. Rather, they are often discovering and creating or improving values as they journey into adulthood. DNA-v helps young people develop strength, overcome unhelpful thoughts, adjust behaviors without attempting to control thoughts and live fully in the present moment, making choices that help them reach their full potential.

ACT-DNA-v has proved effective with adolescents in other settings, however, to enhance its potential for inclusion in mainstream HIV care for adolescents in Uganda, there is a need for exploring its acceptance among HCPs and ALWHA, testing its feasibility and preliminary effectiveness among ALWHA, and potential contextual adaptations to fit the experiences, belief systems and assumptions in Uganda

